#### Emergency Contacts

The final section contains phone numbers young people can call which provide direct access to emergency support both nationally and locally.

#### Study Procedure

The study procedures are summarized in Figure 1. Clinicians will be invited to identify and discuss BlueIce with young people they were working with who meet inclusion criteria. If the young person is interested the clinician will contact the research team and inform them whether the young person has self-harmed in the last 4 weeks.

The research team will arrange to meet with the young people and, if under the age of 16 years, their carers. The study will be discussed, informed consent obtained, and baseline assessments completed. BlueIce will then be downloaded on to the young person’s phone and the sections in the mood lifter personalized.

In order to ensure safety, young people will be instructed to familiarize themselves with BlueIce but not to use it at times of crisis for the next 2 weeks. BlueIce will then be reviewed with the researcher after familiarization to discuss how they found the app and whether they encountered any problems. The young person will then choose to either continue using BlueIce for the next 10 weeks or to stop and have it removed from the phone. If they chose to use BlueIce, they can use it as often as they wish. Follow-up assessments will be completed with young people and the use and acceptability of BlueIce determined.

**Figure 1 figure1:**
[figure not shown]
BlueIce study procedure. CAMHS: Child and Adolescent Mental Health Services; RCADS: Revised Child Anxiety Scales; SDQ: Strengths and Difficulties Questionnaire; MFQ: Mood and Feelings Questionnaire.

### Outcome Measures

#### Mood

Young people and their carers (if under 16 years of age) will complete the Revised Child Anxiety Scales (RCADS) [17-19] and Strengths and Difficulties Questionnaire (SDQ) [20]. These provide an assessment of anxiety, depression, and behavioral problems. Young people will also complete the Mood and Feelings Questionnaire (MFQ) [21], a standardized measure to assess depression. All questionnaires will be completed at baseline and at follow-up after using BlueIce.

#### Safety

Semistructured interviews will be undertaken with young people postfamiliarization and at follow-up. These will focus on safety and in particular whether BlueIce worked as intended (ie, did not crash or freeze) and had no unintentional adverse effects. For example, constantly recording mood as low might increase thoughts of hopelessness and self-harm. Young people will also be asked to rate the extent to which BlueIce might make them self-harm and whether it might help.

#### Acceptability

Although BlueIce was developed with young people who had a lived experience of self-harm, we will assess whether the BlueIce layout and content are understandable and acceptable to those currently in crisis. This will be assessed during postfamiliarization and follow-up interviews and through ratings assessing ease of use, helpfulness, and whether to recommend BlueIce to a friend.

#### Usability

We will assess whether BlueIce can be easily downloaded and personalized on different Android phones. We will also check which parts of the app young people use and which they find most helpful.

#### Self-Harm

Information will be obtained from referring clinicians about whether the young person had been self-harming in the 4 weeks before using BlueIce and in the 4 weeks before the follow-up assessment. In addition, young people will be asked during the follow-up interview whether BlueIce had helped to prevent an episode of self-harm and if so, how many.

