**Methods:**

In this phase I open trial we will evaluate BlueIce, a smartphone app developed and coproduced with young people with lived experience of self-harm. BlueIce includes a mood-monitoring diary, selection of mood-lifting techniques based on cognitive behavior therapy and dialectical behavior therapy, and direct access to emergency telephone numbers. We will recruit young people (n=50) attending specialist child and adolescent mental health services with a current or past history of self-harm to trial BlueIce as an adjunct to their usual care. Questionnaires and interviews will be completed at baseline, postfamiliarization (2 weeks), and at follow-up (12 weeks after baseline) to assess safety, app use, and acceptability. Interviews will be undertaken with clinicians to assess the feasibility of BlueIce within a clinical setting.

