## Discussion

This study seeks to explore the safety, acceptability, feasibility, and use of a smartphone app for young people attending specialist CAMHS who are self-harming. Our study addresses an important problem and through the use of technology aims to empower young people to manage their unpleasant emotions and thoughts of self-harm at times of crisis. A particular strength of our intervention is the coproduction with young people who have a lived experience of self-harm. Young people have shaped the content, design, and appearance of BlueIce in order to ensure that it is acceptable and attractive to our intended users. A further strength of our design is the focus on evaluation and in determining safety. It is important that smartphone apps used as adjuncts to mental health interventions are subject to evaluation [24,25]. In particular, when dealing with sensitive issues such as self-harm, it is important to demonstrate that apps are safe and do not unintentionally cause any adverse events.

To our knowledge, this is the first smartphone app designed with and produced for young people under the age of 18 years who self-harm. Our study design does however have limitations—in particular our reliance on clinical staff to identify and recruit young people. Clinicians have been found to have negative views about eMental health as highlighted in studies looking at clinician attitudes to computerized interventions [26,27]. We are unsure about clinicians’ views about smartphone apps as adjuncts to face-to-face care but are aware that uptake may be limited. We will attempt to minimize this risk through an active process of clinician engagement involving information-giving, demonstrations, and on-going email updates and informal meetings.

A second limitation is our reliance on retrospective self-report to assess the frequency of self-harm. Self-report may underestimate the number of events recalled, particularly for those young people who are engaging in regular and frequent harming. This limitation is acknowledged; although at this stage we are primarily focused on the app functionality and in assessing use, acceptability, and safety. Prospective reporting of self-harm (eg, through diaries) and objective measures of self-harm (eg, accident and emergency attendances) will be considered in a subsequent phase II trial.

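### The only structured record of self-harm after download covers weeks 8 to 12, so an earlier rise that settled could be missed from the safety percentage

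*Protocol article*

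**What the plan says.** Under Outcome Measures, Self-Harm, the protocol article says: "Information will be obtained from referring clinicians about whether the young person had been self-harming". It gives two windows, "in the 4 weeks before using BlueIce and in the 4 weeks before the follow-up assessment". In the same paragraph, young people are asked at follow-up whether the app prevented any episode and, if so, how many.

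The Abstract (Methods) sets the contacts at baseline, "postfamiliarization (2 weeks), and at follow-up (12 weeks after baseline) to assess safety, app use, and acceptability". Study Procedure divides those 12 weeks into 2 weeks of familiarization, during which participants are told "not to use it at times of crisis for the next 2 weeks", and 10 weeks of optional free use. Anyone who chooses to stop at week 2 has the app removed.

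Under Safety, semistructured interviews at weeks 2 and 12 cover whether the app worked and whether it had unintended harmful effects. Participants also rate how far it might make them self-harm and whether it might help. Statistical Analysis defines safety as the share of participants reporting problems, worse mood or more self-harm.

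On the baseline report, Study Procedure describes the referral step as follows: "the clinician will contact the research team and inform them whether the young person has self-harmed in the last 4 weeks". This comes before the research meeting, consent, baseline assessment and download.

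**The concern.** Sample Size calls this a phase I safety trial. The conclusion of the Abstract says the findings on safety, acceptability and use will decide whether a feasibility trial is pursued. An increase in self-harm is one of the three components of the safety percentage. The only item that records whether self-harm occurred after download, by a fixed question over a fixed period, looks back 4 weeks from week 12.

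A 4-week window before and after suits a descriptive comparison of two states. It suits a safety outcome less well, because harm at any time after download counts. If self-harm rose in, say, week 4 and had settled by week 8, the clinician item would not show it. Whether it reached the safety percentage would then depend on the participant raising it in an interview about the effects of the app.

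A second, smaller matter is that the baseline window is tied to referral in one section and to first use in another.

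**Working it through.** **Inputs.** Familiarization 2 weeks and free use 10 weeks (Study Procedure); follow-up 12 weeks after baseline (Abstract, Methods); look-back 4 weeks (Self-Harm). The sample of 50 has no power calculation behind it, so there is no sample-size figure to reproduce.

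**Step 1: the plan's own timeline.** 2 + 10 = 12 weeks, which agrees with the stated follow-up time.

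**Step 2: coverage of the clinician item.** The window runs from 12 − 4 = week 8 to week 12.

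- Share of time since download: 4/12 = 33% covered, 8/12 = 67% outside.
- Share of free use, for those who continue: 4/10 = 40% covered, 6/10 = 60% outside.
- For a participant who stops at week 2, the app is on the phone in weeks 0 to 2 only, and the window overlaps that period by 0 weeks.

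**Step 3: what else could record self-harm in weeks 0 to 8.**

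| Source | Timing | Described content | Records episodes? |
|---|---|---|---|
| Safety interview | week 2 | function, unintended effects, ratings of possible harm and help | Not described as doing so |
| Safety interview | week 12 | the same, with no stated 4-week limit | Not described as doing so |
| Young person's episode question | week 12 | episodes the app prevented | Benefit only |
| Clinician report | week 12 | self-harm, yes or no, weeks 8 to 12 | Yes, but outside weeks 0 to 8 |

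Earlier harm can be reported, but no source asks everyone about it in the same way.

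**Step 4: illustration of what a 4-week window leaves out.** Assume, for illustration only, that each participant has the same constant risk p of at least one episode in any 4-week period, independent between periods. Then the risk over 12 weeks is P = 1 − (1 − p)³. Among participants with any episode in weeks 0 to 12, the share with none in weeks 8 to 12 is (P − p)/P.

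| p (assumed) | P | Share with none in weeks 8 to 12 |
|---|---|---|
| 10% | 0.271 | 63% |
| 25% | 0.578 | 57% |
| 50% | 0.875 | 43% |
| 75% | 0.984 | 24% |

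These figures concern any episode, not an increase. The protocol article gives no rate, so they show only how the gap behaves over a range.

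**Step 5: the baseline anchor.** If referral precedes download by L weeks, a window taken at referral overlaps the 4 weeks before use by 4 − L weeks. For assumed L = 0, 1, 2 or 4, the overlap is 4, 3, 2 or 0 weeks. The documents do not give L.

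**The case against.** The strongest reply is that a reader might infer that self-harm in weeks 0 to 8 is not captured at all, and the protocol article does not support that. The week-2 interview falls inside that period. Both interviews cover unintended harm with no 4-week limit, and the Safety section gives increased thoughts of self-harm as an example of what they look for. Statistical Analysis bases the safety percentage on what participants report and does not tie it to the clinician item. This part of the reply stands: an early rise could be reported. What remains is that the described questions concern effects of the app. A participant who self-harmed more but did not connect it with the app has no described prompt to say so.

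Other stronger readings also fail:

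- **Harm would be expected early.** No section says so, and the mechanism offered, repeated recording of low mood, could build up over time.
- **The two windows are not comparable.** They match in length and informant. Only the baseline anchor is in doubt, and the report at referral may simply serve to classify eligibility as current or past self-harm.
- **Exposure is 12 weeks for everyone.** The first 2 weeks exclude use in crisis, and some participants may stop at week 2.
- **Leaving out emergency attendances is an error.** The Discussion discloses the choice: "objective measures of self-harm (eg, accident and emergency attendances) will be considered in a subsequent phase II trial". It is a stated limit of a small, uncontrolled, descriptive study.

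The full interview schedule may also contain more than an article shows. That could narrow the point in practice, but it does not alter the window that the article fixes for the clinician report.

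**Conclusion.** The point holds in a limited form. The structured measure of self-harm occurrence after download covers weeks 8 to 12: 33% of the time since download, or 40% of free use for those who continue. Weeks 0 to 8 depend on semistructured interviews described as asking about effects of the app, and the only episode count is of episodes prevented. A rise that began and settled before week 8, and that the participant did not attribute to the app, could be missed from the safety percentage.

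The coverage figures follow from the stated timeline and need no assumption. The shares in the illustration rest on an assumed constant risk and are not estimates for this trial. How often such a rise would occur cannot be told from the documents.

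On the baseline window, the finding is only that Study Procedure and Self-Harm must be reconciled. The size of any mismatch is unknown.

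A related limit supports the wording of the fix. A yes/no report cannot show an increase in someone already self-harming at baseline. The Discussion, for its part, describes self-harm as measured by self-reported frequency, whereas the Self-Harm section describes clinician-reported presence or absence.

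**What to change.** 1. Keep both 4-week windows for the before/after description.
2. Add one question on any self-harm since download, and any increase in its frequency or severity. Put it to the young person at the week-2 and week-12 interviews and to the clinician at the planned follow-up contact. Ask it without reference to whether the app was the cause. Coverage rises from 4/12 to 12/12 weeks.
3. Use the answers for the increase-in-self-harm part of the safety percentage.
4. Give one anchor date for the baseline 4-week window and use it in both Study Procedure and Self-Harm. If the report at referral is the only one obtained, say so and give the observed interval from referral to download.

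The cost is one question at contacts already planned, and longer recall (up to 12 weeks), which may under-count episodes. The Results section says that recruitment is complete and post-use assessments are under way. The week-2 question may therefore no longer be possible for most participants, and step 2 would then apply to the remaining week-12 contacts. If the question can no longer be added, the report should say that the clinician measure covers weeks 8 to 12 only and limit the safety conclusion accordingly.

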#### Feasibility

This will be assessed through the number of referrals per team and professional group and through interviews with referring clinicians. We will also undertake qualitative interviews with clinicians to determine usability, usefulness, and fit with clinical practice.

### Sample Size

This is an initial feasibility study and as such no formal power calculation was undertaken. For this phase I safety trial we plan to recruit 50 young people, a sample that will be sufficient to reach saturation through analysis of data collected in semistructured interviews [22].

### Statistical Analysis

We will describe the cohort in terms of age, gender, and previous self-harm and report recruitment, completion, and drop-out rates. Safety will be assessed by the percentage of participants who report problems, a worsening of mood, or an increase in self-harm. Mean and standard deviations of ratings (potential harm and help) will be reported.

Acceptability will be determined by satisfaction ratings and through analysis of semistructured interviews. Interviews will be audiorecorded and transcribed. They will then be analyzed using a predefined framework derived from the interview schedule and adapted and revised on the basis of participant responses [23]. The interviews will also assess usability and how often young people used the app and which features.

Feasibility will be assessed by examining referral flows by teams and professional groups. We will also interview referring clinicians to obtain their views about usability, usefulness, and fit with clinical practice.

Outcome data from standardized questionnaires and reported changes in self-harm will be treated as preliminary and will not be subject to extensive analysis. We will conduct an exploratory analysis using descriptive statistics, where appropriate, to report pre- and post-use changes.

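### The rating of how far BlueIce might cause self-harm is summarised only by mean and SD, and episodes prevented are counted with no stated counterpart for episodes provoked

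*Protocol article*

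**What the plan says.** All references are to the protocol article.

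- **Outcome Measures, Safety.** Young people are interviewed about safety after familiarization and at follow-up, including about unintended adverse effects. They also "rate the extent to which BlueIce might make them self-harm and whether it might help". Both ratings are hypothetical in wording.
- **Outcome Measures, Self-Harm.** Referring clinicians say whether the young person was self-harming in two 4-week windows, one before using the app and one before follow-up. At the follow-up interview the young person is also asked "whether BlueIce had helped to prevent an episode of self-harm and if so, how many".
- **Statistical Analysis.** "Safety will be assessed by the percentage of participants who report problems, a worsening of mood, or an increase in self-harm". The next sentence fixes the summary of the two ratings: "Mean and standard deviations of ratings (potential harm and help) will be reported".
- **Sample Size.** "For this phase I safety trial we plan to recruit 50 young people". The number rests on qualitative saturation, with no power calculation.
- **Results.** Recruitment is complete and post-use assessments are in progress.

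**The concern.** There are two linked weaknesses in how self-harm that the young person attributes to the app is captured and reported.

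First, most ratings of whether an app might make someone self-harm can be expected to sit at or near the lowest value. That is a reasonable expectation, not something the article documents. If it is right, the safety reader needs to know how many people rated above the lowest value and how far above. A mean and SD do not give that.

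Second, help has two app-attributed measures, a rating and a count of episodes prevented. App-attributed harm has a rating but no stated count of episodes the app led to or worsened. A report with a number of prevented episodes and no number of provoked ones leaves the reader unable to set one against the other. The article itself treats provoked harm as possible: the Safety section gives the example that repeatedly recording low mood might feed hopelessness and self-harm.

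**Working it through.** **Is there a plan figure to reproduce?** No. The Sample Size section states "This is an initial feasibility study and as such no formal power calculation was undertaken", so there is no error rate, effect size or SD to check. The arithmetic below is illustrative.

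**Inputs.** n = 50 is the recruitment target in the Sample Size section; the number actually giving a rating may differ. The rating scale is not given, so 0 to 10 is assumed, with 0 to 5 as a check. The four response patterns are invented.

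**Formulas.** Mean = Σx/n. SD = √[(Σx² − n·mean²)/(n − 1)]. Exact (Clopper-Pearson) 95% limits for k of n are the 0.025 quantile of Beta(k, n − k + 1) and the 0.975 quantile of Beta(k + 1, n − k).

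| Pattern (n = 50) | Mean | SD | Above lowest rating | At maximum |
|---|---|---|---|---|
| A: 48 at 0, 2 at 10 | 20/50 = 0.40 | √[(200 − 8)/49] = 1.98 | 2/50 = 4% | 2 |
| B: 40 at 0, 10 at 2 | 20/50 = 0.40 | √[(40 − 8)/49] = 0.81 | 10/50 = 20% | 0 |
| C: 47 at 0, 3 at 10 | 30/50 = 0.60 | √[(300 − 18)/49] = 2.40 | 3/50 = 6% | 3 |
| D: 20 at 0, 30 at 1 | 30/50 = 0.60 | √[(30 − 18)/49] = 0.49 | 30/50 = 60% | 0 |

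Exact 95% intervals: 2/50 gives 0.5% to 13.7%, and 3/50 gives 1.3% to 16.5%.

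On a 0 to 5 scale, 2 of 50 at the maximum gives mean 10/50 = 0.20 and SD √[(50 − 2)/49] = 0.99. The percentage is still 4%.

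**Reading.** A and B share a mean, as do C and D. The SD separates the pairs but does not tell the reader that two or three people chose the top value. The percentage above the lowest rating is not enough alone either: it is larger in B than in A, although only A has anyone at the maximum. The full frequency table resolves both.

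**Do the other planned safety summaries fill the gap?**

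1. The percentage with an increase in self-harm is a change from before to after. It does not record whether the young person attributes an episode to the app.
2. The clinician item asks whether self-harm occurred in each window. If that yes/no item is the source, someone already positive at baseline cannot register an increase. Young people who are currently self-harming are eligible (Setting and Participants).
3. With follow-up 12 weeks after baseline, the second window covers the last 4 weeks. The first 12 − 4 = 8 weeks fall outside it. No such window is stated for the prevention question.
4. The interviews on adverse effects may bring provoked episodes to light. The article states no count of them, whereas it does state a count of prevented ones.

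**The case against.** The strongest reply is that harm is already reported per participant. The sentence just before the one on means and SDs plans the percentage with problems, worse mood or more self-harm, and interviews at two visits ask about adverse effects. This stands. A reader might infer that participants who are harmed vanish into an average, or that the hypothetical rating is the only measure of harm; the article supports neither.

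A reader might also infer that harm and help are measured in wholly different ways. They are not: both ratings share the same hypothetical wording and the same summary. The difference lies only in the additional count of prevented episodes. Nor is that count listed among the safety criteria, and the article treats reported changes in self-harm as preliminary, so it would be too strong to say that the safety conclusion itself is biased.

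The interview schedule is not shown and may already contain the mirror question. This stands, and the recommendation is conditional on it. The article did, however, choose to name the benefit count as an outcome and named no counterpart.

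Finally, a frequency table could be left to an analysis plan, and nothing forbids one. That is fair, but the article does fix a summary for these ratings, and the one it fixes suits a safety item poorly. The objection that the scale and patterns are assumed is also correct. They show what the mean and SD leave open, not what the data will look like.

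**Conclusion.** The point holds in a limited form. The stated summary of the app-attributed harm rating does not show how many young people gave a raised rating, and the other planned safety summaries do not report that rating per participant. The article also states a count of prevented episodes with no counterpart for episodes led to or worsened.

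This is a modest weakness in reporting and measurement; it does not invalidate the safety assessment. Its possible size can only be illustrated: on an assumed 0 to 10 scale with 50 raters, a mean of 0.40 fits either 2 people at the maximum (4%, exact 95% CI 0.5% to 13.7%) or none there and 10 people at 2. The conclusion rests on ratings clustering near the lowest value, on a scale the article does not give, and, for the second part, on the unseen interview schedule not already asking about provoked episodes.

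**What to change.** **Statistical Analysis.** Report the number of participants at each harm and help rating, at each visit where the ratings are collected, with the number who answered. Give the percentage above the lowest harm rating with its exact 95% CI. Keep the mean and SD beside these. This uses data already being collected and costs one table.

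**Self-Harm.** Unless the interview schedule already does so:

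- in the remaining follow-up interviews, ask directly after the prevention question whether BlueIce led to or worsened an episode of self-harm and, if so, how many;
- code the transcripts of completed interviews for such episodes;
- report the prevented and provoked counts side by side, stating for how many participants the harm question was actually asked.

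**Cost.** One interview item and some transcript coding. Because post-use assessments are already under way, the provoked-episode count may be incomplete: an episode that was never asked about may not appear in a transcript. The report should say so and should not read a missing mention as zero.
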